### Detailed methods

**Plasma proteomics:** The SomaScan assay that uses SOMAmer (Slow Off-rate Modified Aptamers) reagents to selectively bind and quantify proteins
^
61
^ will be used for plasma proteomics profiling. The SomaScan Assay quantitatively transforms the protein epitope availability in a biological sample into a specific SOMAmer-based DNA signal. A SOMAmer-protein binding step is followed by a series of partitioning and wash steps to convert relative epitope concentrations into measurable nucleic acid signals that are quantified using DNA-hybridisation microarrays. Briefly, diluted plasma samples are incubated with the respective SOMAmer reagent mixes that have been attached to streptavidin (SA)-coated beads (catch 1). Each of the SOMAmers is synthesized with photo-cleavable biotin, a spacer and cyanine-3 fluorophore at the 5’ end. The beads are washed to remove non-specifically associated proteins and other matrix constituents. Proteins that remain bound to SOMAmer reagents are labelled using an NHS-biotin reagent. SOMAmer complexes and unbound SOMAmer reagents are released from the SA beads using ultraviolet light that cleaves the photo-cleavable linker within the SOMAmer reagent construct into a solution containing an anionic competitor (biotin originally incorporated in the SOMAmer is left on the SA beads). Non-specific interactions, which have much faster dissociation rates compared to specific interaction, dissociate, and the polyanionic competitor solution prevents them from rebinding while specific complexes are maintained. The photo-cleavage eluate, which contains all SOMAmer reagents (some bound to a biotin-labelled protein and some free), is separated from the beads and then incubated with a second streptavidin coated bead that binds protein-SOMAmer complexes through biotin on the protein (catch 2). The inversion of polarity of attachment of protein-SOMAmer complexes on the second set of SA beads contributes a substantial degree of additional specificity enhancement by dramatically minimizing non-specific interactions due to multivalent interactions between proteins and SOMAmer-coated SA beads in the first (catch 1) incubation. The free SOMAmer reagents (which no longer contain biotin) are removed during subsequent washing steps. In the final elution step, protein-bound SOMAmer reagents are released from their proteins using denaturing conditions and recovered. These SOMAmer reagents are then quantified by hybridisation to custom DNA microarrays. The cyanine-3 signal from the SOMAmer reagent is detected on microarrays. The readout in relative fluorescent units (RFU) is directly proportional to the amount of target epitope in the initial sample. The resulting measurement and quantitation of ~7000 plasma proteins presented in a proprietary text-based format called ADAT. The

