^. The faecal sample undergo a lysate preparation process that includes mechanical disruption (bead beating), removal of inhibitors, purification and elution of DNA and RNA using spin columns. The extracted total nucleic acid is then used for testing. 40 µL of total nucleic acid extract is mixed with 50 µL of AgPath One Step RT-PCR buffer and 4 µL of enzyme mix (Life Technologies) in a 100 µL reaction, then loaded onto the microfluidic card by centrifugation at 1,200 rpm, 1 min for twice, followed by sealing and cutting off the loading ports. The cards are analysed in a ViiA7 or QuantStudio 7 Flex instrument (Life Technologies, USA). The cycling conditions are set as follows: 45°C for 20 minutes and 95°C for 10 minutes, followed by 40 cycles of 95°C for 15 s and 60°C for 1 minute. Extrinsic controls (MS2 bacteriophage and Phocine herpesvirus) are added to each sample during the lysate preparation to evaluate extraction and amplification efficiency while blank controls help rule out contamination during the extraction process. The assay uses predefined thresholds although the baseline for each target may require adjustment. A sample is deemed positive for a particular target when an appropriately shaped amplification curve crosses the analytical threshold for positivity before or at cycle 34.9 and negative if the curve does not cross the threshold line or crosses the threshold line at cycle 35.0 or later. Pathogen quantities in copy number are derived based on the standard curve for each target.

**Faecal biomarkers of enteropathy: Stool** myeloperoxidase, alpha-1-antitrypsin, and calprotectin will be quantified using the ELISA assay (Immundiagnostik AG, Germany) according to manufacturer’s instructions. The absolute concentration of the three biomarkers in samples will be calculated for 15 mg of stool using a dose response curve generated from the manufacturer’s standards.

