### Statistical analysis

**
*Descriptive analysis.*
** The distribution and prevalence of biomarkers in laboratory assays which have clear clinical interpretations will be described at admission and discharge timepoints across the nutritional strata and compared with community participants. These more targeted assays will include the serum micronutrients, serum aflatoxin biomakers, plasma lipopolysaccharides, haemoglobin variants, faecal biomarkers of enteropathy, and faecal pathogens. For these assays, the crude and confounder adjusted case fatality rates, which will be appropriately weighted for selection into the NCC analysis and the original CHAIN cohort, will be described.

The appropriate non-parametric statistical test will be employed to calculate the significance of the association between each feature and each outcome or measure of interest in every relevant subset of patients. For binary outcomes (i.e., the primary outcome of mortality), the Wilcoxon rank sum test will be used to determine the significance of the association while Hedge’s g will be used to calculate the effect size of the difference between groups. For continuous measures, the Spearman’s rank correlation coefficient will be used to assess the strength and significance of the association between the feature and the measure. Linear regression models will be fit for each feature against the confounding variables of interest and the residuals taken as the confounder-adjusted features.

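### For mortality, a rank test is paired with Hedges' g on an unstated scale, so the reported size and direction of an association need not match the test beside it

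*Protocol article*

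**What the plan says.** The protocol article, Statistical analysis (Descriptive analysis), sets a general rule for univariate work: "The appropriate non-parametric statistical test will be employed to calculate the significance of the association between each feature and each outcome". For binary outcomes, with mortality named as the primary one, the Wilcoxon rank sum test is "used to determine the significance of the association while Hedge’s g will be used to calculate the effect size of the difference between groups". With continuous measures one rank statistic does both jobs: "the Spearman’s rank correlation coefficient will be used to assess the strength and significance of the association between the feature and the measure". Confounder adjustment is by residuals: "Linear regression models will be fit for each feature against the confounding variables of interest and the residuals taken as the confounder-adjusted features". The section gives no scale for g or for these regressions.

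The Detailed methods describe the assay outputs:
- **Proteins:** "The readout in relative fluorescent units (RFU) is directly proportional to the amount of target epitope in the initial sample".
- **Enteric pathogens:** "Pathogen quantities in copy number are derived based on the standard curve for each target". A target whose curve does not cross the threshold before cycle 35 is negative.
- **Lipids:** intensities below three times the blank are recorded as zero concentration.
- **Aflatoxin-albumin:** there is a stated limit of detection.

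The only mention of transformation concerns handling of the proteomics files, and its kind is not given.

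**The concern.** A rank test asks whether a child who died tends to have a higher value than a survivor. Hedges' g asks how far apart the arithmetic means are in SD units. For near-symmetric features with similar spread the two answers agree. For features spanning orders of magnitude, or with many zeros, a few extreme children set both the means and the pooled SD, and the answers can part.

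What is at stake is the size and direction printed beside each p-value. Two features that separate deaths from survivors equally well by rank could carry very different g values only because one is more skewed. In harder cases a feature ranked significantly higher in deaths could show g near zero or negative. The plan avoids this mismatch for continuous measures by using Spearman throughout, so it arises only for binary outcomes, which include the primary one.

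**Working it through.** **Inputs from the article:** 350 deaths and 658 survivors (Study design), the Wilcoxon test and Hedges' g (Statistical analysis). The article states no value of g and no feature distributions, so there is no figure of its own to reproduce. All distributions below are assumptions.

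**Formulas**
- Rank effect: AUC = U/(n1·n0). Cliff's delta = 2·AUC − 1.
- g = J·(mean1 − mean0)/s_p, with s_p² = (349·s1² + 657·s0²)/1006 and J = 1 − 3/(4·1006 − 1) = 0.999.

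**1. Equal rank separation, different skew.** Features are log-normal with equal log-SD in both groups and a shift of 0.5 log-SD. The AUC is Φ(0.5/√2) = Φ(0.354) = 0.638 at every skew (Cliff's delta 0.276), and the median Wilcoxon p is about 5e-13.

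| Log-SD | g, untransformed | Wrong sign | g, log scale |
|---|---|---|---|
| 0.25–0.3 | 0.50 | 0% | 0.50 |
| 0.5 | 0.48 | 0% | 0.50 |
| 1 | 0.40 | 0% | 0.50 |
| 1.5 | 0.30 | 0.1% | 0.50 |
| 2 | 0.22 | 0.7% | 0.50 |
| 3 | 0.14 | 5.1% | 0.50 |

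Hand check at log-SD 1:
- Means are e^0.5 = 1.649 (survivors) and e^1 = 2.718 (deaths), a difference of 1.070.
- SDs are 1.649·√(e − 1) = 2.161 and 2.718·√(e − 1) = 3.563.
- Pooled variance is (349·12.70 + 657·4.67)/1006 = 7.45, so s_p = 2.73 and g = 1.070/2.73 = 0.39. This agrees with the simulation.

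**2. Unequal spread.** Survivors have log-SD 2, and the deaths' log mean is 1 unit higher.
- Deaths' log-SD 1.5: AUC 0.655, median g 0.05, wrong sign in 27% of samples.
- Deaths' log-SD 1: AUC 0.673, median g −0.10, wrong sign in 99.7%. This is not sampling noise. The arithmetic means are e^(1 + 0.5) = 4.48 in deaths and e^2 = 7.39 in survivors, so means and ranks point in opposite directions.
- Log-scale g is 0.54 and 0.58 respectively, with no wrong sign.

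**3. Zero-heavy pathogen.** Detection is 45% in deaths and 30% in survivors, positive values have the same distribution in both groups, and negatives are coded zero. The AUC is 0.45·0.70 + 0.5·(0.45·0.30 + 0.55·0.70) = 0.315 + 0.260 = 0.575, and the median Wilcoxon p is about 3e-6 to 5e-6.

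| SD of log10 copies among positives | g, untransformed | Wrong sign |
|---|---|---|
| 0.5 | 0.14 | about 2% |
| 1.0 | 0.05–0.06 | 25–28% |
| 1.5 | 0.03 | 41–43% |

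Ranges show variation between repeated simulations. On log10(copies + 1), g is about 0.30 with no wrong signs. The AUC is unchanged by any monotone transformation.

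**The case against.** **A reader might infer that the plan commits to raw-scale g.** It does not. The article neither states nor excludes a transformation, g can be computed on log values, and per-assay pre-processing is a detail that a condensed article may leave to a fuller plan. This stands, so every numerical consequence above is conditional. It does not remove the mismatch: even on a log scale, g is a mean-based measure whose value for zero-heavy features depends on how zeros are coded.

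**A reader might infer that wrong signs are to be expected across all modalities.** The documents give no distributions that would show this. Reversal needs heavy tails, many zeros or unequal spread. Endotoxin is read over a stated range of 0.01 to 1.00 EU/ml, which limits its tail, and the article does not say that negative pathogen results enter as zero copies. This also stands.

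**A reader might infer that g decides which biology is called important.** No section gives it that role. Enrichment starts from features significantly associated with the outcome, modalities are combined by a meta-learner, and classifiers are judged by AUROC and AUPRC. The article does not say that g defines the up/down split before enrichment.

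**Pathogen detection will be described anyway.** Distribution and prevalence are planned for the targeted assays, so a pathogen would not necessarily look null. That softens the concern for pathogens only.

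**A reader might infer that g cannot be compared between modalities at all.** That is too strong. It is unit-free, and in the equal-spread scenarios log-scale g stays near 0.50 whatever the skew. The distortion belongs to untransformed g.

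**Conclusion.** The point holds in limited form. For binary outcomes the plan names an effect measure that does not correspond to its test and fixes no scale for it, although the outputs it describes include linear and zero-coded quantities. If g is computed on untransformed values, one rank separation (AUC 0.64) can be reported as anything from 0.50 to 0.14 by skew alone. Under the assumed heavy-tailed, zero-heavy or unequal-spread distributions, g can be near zero or opposite in sign. For moderately skewed features without zeros and with similar spread (log-SD of 1 or less) the loss is modest, 0.40 to 0.50, and the sign is safe. P-values, significance calls and the predictive models' AUROC and AUPRC do not depend on g. The severity is minor to moderate.

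**What to change.** For binary outcomes, make the reported effect size U/(n1·n0), that is, the probability that a child who died has a higher value than a survivor, counting ties as half (or Cliff's delta), with a confidence interval. This matches the use of Spearman for continuous measures.

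If Hedges' g is kept, state that it is computed only after a log or rank-based inverse-normal transformation, with the handling of zeros and values below detection fixed in advance for each assay. State the scale used for the residual adjustment as well. For pathogens, report detection and log10 copies among positives separately.

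The change takes a sentence or two of analysis text and no new data, since U is already computed for the test. The price is one more reported column and a metric less familiar to some readers.

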### Study design

A nested case-cohort design drawing from a larger cohort provides estimates that are representative of the entire cohort while also yielding slightly more statistical power than a case control design
^
58
^. Case-cohort selection involves a random subsample of the original cohort (sub-cohort), independently of how cases are defined, followed by additional inclusion of all cases outside the sub-cohort creating the case-cohort set
^
59
^. This results in overrepresentation of the cases in the case-cohort set compared to the original cohort which is dealt with in analysis by weighting. A further advantage of this design over a case-control design is that the sub-cohort can also be used in analysis of other outcomes. In CHAIN, this could include outcomes of readmission or growth among survivors in future analyses, as well comparisons between acutely ill children and community children and between nutritional strata among acutely ill children in the current analysis.

The original CHAIN cohort stratification was maintained in the CNCC design; thus, a random 24% sub-cohort of children enrolled in the CHAIN cohort stratified by site was selected. This included 658 survivors (sub-cohort non-cases) and 109 deaths (sub-cohort cases). Thereafter, all remaining deaths (n=241 cases) that were not selected in the random 24% sub-cohort (
Figure 3) were added, giving a total of 350 cases. An additional 30 randomly selected community participants from each site (total N=270) were chosen.

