### Sample size

Multiple studies in both low- and high-income settings indicate a prolonged increased mortality risk after admission (including >1 year) compared to the community peers
^
10,
43,
60
^ which is now considered a well-recognised phenomenon. The primary analyses will be of acute mortality occurring within 30-days from admission and post-discharge mortality within 180-days from discharge using samples collected at admission and discharge timepoints. Power and effect size are a function of the number of cases, correlation between cases and survivors, and the ratio of cases to survivors. It is likely that the strength of association between exposures of interests and death will vary in magnitude between the 30-day and 180-day mortality periods. Sample size calculations suggest that a ratio of one case to two non-cases is adequate to reliably detect an HR of 1.5 at >80% power. The design selected all available deaths and simulation-based power calculations suggested that adding more non-cases per cases would yield minimal gains in power while incurring substantial additional expense.

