### Laboratory analyses

The full laboratory protocol is described in the
*detailed methods* section. Briefly, the aptamer based SomaScan assay will be used to quantify ~7000 proteins in plasma
^
61
^. We will also apply both targeted and untargeted mass spectrometry-based approaches to quantify metabolites including amino acids, acylcarnitines, biogenic amines, lipids, sugars, vitamins and minerals in serum
^
62–
64
^. Lipopolysaccharide levels in plasma will be measured via a limulus amoebocyte lysate-based, quantitative chromogenic endpoint assay
^
65
^. The gut microbiome will be determined through metagenomic sequencing of DNA extracted from stool samples. Further, faecal biomarkers of enteropathy including myeloperoxidase, alpha-1-antitrypsin, and calprotectin will be quantified in stool using ELISA. We will use quantitative polymerase chain TaqMan Array Card based assay
^
66
^ to test for a custom panel of 35 common enteric pathogens using nucleic acids extracted from rectal swabs. Finally, we will quantify haemoglobin variants using dried blood spots and aflatoxin-albumin
^
67–
69
^ in serum samples.

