### Adjustment for multiple comparisons

All
*p*-values will be corrected for multiple hypothesis testing using Bonferroni’s correction where appropriate. In brief, the raw
*p*-value will be multiplied by the total number of statistical tests performed to generate the adjusted
*p*-value.

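### Adjusting by taking feature residuals on the confounders, with death left out of that regression, shrinks the adjusted died-versus-survived differences toward zero

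*Protocol article*

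**What the plan says.** Protocol article, Statistical analysis (Descriptive analysis): for death, "the Wilcoxon rank sum test will be used to determine the significance of the association" and "Hedge’s g will be used to calculate the effect size of the difference between groups". Continuous measures are handled by Spearman correlation. The paragraph closes with the adjustment rule: "Linear regression models will be fit for each feature against the confounding variables of interest and the residuals taken as the confounder-adjusted features". Death does not enter that regression and is not itself residualised, and no model holding feature, confounders and death together is named for these tests.

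The same section promises confounder-adjusted case fatality rates for the targeted assays, weighted for selection. These are not described as residual-based.

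Adjustment for multiple comparisons: p-values are "corrected for multiple hypothesis testing using Bonferroni’s correction where appropriate". Laboratory analyses: "the aptamer based SomaScan assay will be used to quantify ~7000 proteins in plasma". Study design: all deaths are included, "giving a total of 350 cases", alongside 658 survivors, and over-representation of deaths is to be handled by weighting. Whether that weighting covers the residualising regressions is not stated.

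**The concern.** A variable that confounds the feature–death relation predicts death. When the feature is regressed on such variables alone, their slopes pick up some of the feature's own link with death, and subtracting the fitted values removes it. What remains is a diluted contrast.

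The Introduction reports that nutritional status, illness severity, HIV, pre-existing conditions and household factors were associated with mortality in this cohort. If the confounder set draws on these, R² is above zero.

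Two things are at stake. Adjusted effect sizes would be too small, and beside the crude values they would make confounding look stronger than it is. Power would also fall at a strict Bonferroni threshold, and the pathway enrichment step starts from the proteins found significant. The study's purpose is mechanistic discovery, so missed signals are a real cost.

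**Working it through.** **The plan's own power figure.** The Sample size section says that "a ratio of one case to two non-cases is adequate to reliably detect an HR of 1.5 at >80% power". Alpha, sidedness and exposure distribution are not given. Assume two-sided 0.05 and a binary feature present in half the children:
- Schoenfeld with 350 deaths: √(350 × 0.25) × ln 1.5 = 3.793, and Φ(3.793 − 1.960) = 96.7%.
- With an assumed sampling efficiency of 1.88/2.88 (658/350 = 1.88 survivors per death): 3.793 × √0.653 = 3.065, and Φ(1.105) = 86.5%.
- At 20% exposure the two figures are 85.9% and 68.8%.

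So power above 80% is attainable but cannot be strictly reproduced. The figure concerns a hazard ratio and says nothing about the residual method.

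**The attenuation.** Write the joint least-squares fit of feature X on death Y and confounders C as X = a + βY + γC + e. The residual of X on C alone is r = βY* + e, where Y* is the residual of Y on C. The died-minus-survived mean of r is cov(r, Y)/var(Y) = β · var(Y*)/var(Y) = **β(1 − R²)**. This is an identity: simulated data sets matched it with a maximum deviation below 10⁻¹⁴.

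**Type I error and power.** The residual t statistic is about √(1 − R²) times the joint one.
- Type I error at nominal 5% is 2Φ(−1.96/√(1 − R²)): 4.4%, 3.9%, 2.8% and 1.9% at R² 0.05, 0.10, 0.20 and 0.30. Simulated Wilcoxon rates were 3.9%, 2.6% and 2.0% at R² of about 0.05, 0.19 and 0.31.
- Power is Φ(ncp − z/√(1 − R²)), against Φ(ncp − z) for the joint linear model.

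Inputs: 350 deaths and 658 survivors, so 350 × 658/1008 = 228.47; z = 4.489 for two-sided 0.05/7000 (the 0.05 is assumed). A true shift of 0.35 SD and the R² range are also assumptions. Example at R² 0.10:
- ncp = 0.35 × √(228.47 × 0.90) = 5.019.
- Joint: Φ(0.530) = 70%.
- Residual: Φ(5.019 − 4.732) = 61%.

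| R² | Effect multiplied by | Joint, formula | Residual mean test, formula | Joint, simulated | Residual Wilcoxon, simulated |
|---|---|---|---|---|---|
| 0.05 | 0.95 | 75% | 71% | – | – |
| 0.10 | 0.90 | 70% | 61% | 70% | 55–56% |
| 0.17 | 0.83 | 63% | 46% | 61–63% | 38–42% |
| about 0.25 | 0.75 | 54% | 27% | 53–55% | 25% |

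Ranges are across separate simulations (one normal confounder, unweighted slopes; confounder AUROC 0.69, 0.75 and 0.80 in the last three rows). Part of each simulated gap is Wilcoxon against t-test. It was 2–3 points when confounders did not predict death, and about 4–6 points when a t-test was run on the same residuals at the tabulated settings.

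**Weighted slopes.** Weighting back to the cohort (350/3101 deaths instead of 350/1008) lowers the relevant R² from about 0.17, 0.24 and 0.33 to 0.08, 0.12 and 0.18 at AUROC 0.75, 0.80 and 0.85. Simulated Wilcoxon power was then about 66%, 57% and 50% at AUROC 0.69, 0.75 and 0.80. The effect is still multiplied by 1 minus the weighted R².

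**The case against.** The best reply is that the size is unknown. The article names no confounder set. With weak confounders (R² 0.05 or less), a joint test with 80% power would lose only about 1.5 points at 0.05 and 3.4 at 0.05/7000. This stands. So does the point on weighting: if the residualising slopes are weighted, most of the power comes back. Pooling all 350 deaths also matches neither primary analysis (30-day and post-discharge mortality), so the power figures illustrate and do not predict. The 0.05/7000 threshold suits the proteome; targeted assays corrected separately would face a milder one. That the residuals feed the Wilcoxon and Hedges' g step is the natural reading but is not spelled out.

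Some stronger readings are tempting but unsupported:
- That every adjusted result in the study is biased. The adjusted case fatality rates are not described as residual-based.
- That the bias is worst for the most confounded features. The factor depends only on death and the confounders, so with the same sample and confounder set all features shrink equally and the order of their mean differences is kept.
- That residualising leaks test data into the prediction models. The Integrated analysis and Stacked generalization sections never say that residuals enter them.
- That true mechanisms will be dismissed. The error is conservative and may be small.

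None of this removes the identity.

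**Conclusion.** The point holds as a should-fix. Followed as written and on its natural reading, the rule gives residual-based adjusted effects multiplied by (1 − R²) and a test that rejects too rarely. Confidence is high for the direction and not for the size. Attenuation is about 5%, 10%, 17% and 25% at R² 0.05, 0.10, 0.17 and 0.25 with unweighted slopes. The power loss is minor at the low end and large under Bonferroni at the high end. This rests on an assumed R² range, an assumed 0.35 SD shift and unweighted slopes. False-positive risk is not raised with unweighted slopes.

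**What to change.** Replace the residual step with one model per feature that contains death and the confounders together, and report the adjusted coefficient with its test. Either form works:
- the feature (rank- or log-transformed if needed) regressed on death plus confounders; or
- logistic or Cox regression of death on feature plus confounders, with case-cohort weights where cohort-level estimates are wanted.

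For continuous measures, regress the measure on feature plus confounders, or use a partial rank correlation.

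The cost is wording, code and slightly more modelling; no new samples or data are needed. There is a trade-off in power. In one simulation at AUROC 0.75, 0.80 and 0.85, weighted logistic regression with robust variance had 50%, 41% and 29% power, against 57%, 52% and 42% for the joint linear model. It still beat unweighted residuals (35%, 23% and 9%) but not weighted ones (55%, 49% and 40%), whose effect estimates remain attenuated. The joint linear model is therefore the natural choice for screening features, with weighted models for estimates meant to describe the cohort.
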